#### Secondary outcome measure

*Physical activity level*. The physical activity level of the participants will also be measured as secondary data to examine its relationship to cognitive functions as suggested by previous studies [22, 23]. It will be measured using accelerometers (i.e. GT3X). The data used for analysis are the times spent in sedentary activity and MVPA based on the default energy expenditure algorithm in the accelerometer device [24]. The day (0700–2100) will be considered invalid if the wear time is less than 10 hours and will then be excluded from the analysis.

### Sample size calculation

Previous study [13, 14] showed physical exercise had notable effects (corresponding to a Cohen’s *d* of about 0.9) on improving sleep onset latency, sleep duration and sleep duration. We assumed that melatonin supplements have similar effects on sleep. A sample of 20 participants per group is computed by G*power software to achieve a power of 80% and a level of significance of 5% and 95% confidence level. Assuming 25% attrition rate, 25 participants per group will be recruited (i.e. the total number is 100).

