Over the past decade, a significant body of research has investigated the effects of physical exercise on sleep and the results generally supported the positive impact of physical exercise on sleep (see Kelley et al. [12] for review). Previous studies also support the sleep benefits of physical exercise in children with ASD. For example, we have examined the impact of a basketball training intervention on sleep quality (sleep efficiency and wake after sleep onset) and cognition (inhibition control and working memory) in 40 children with ASD [13]. Research revealed a significant improvement in sleep efficiency and reduction in wake after sleep onset time in the intervention group but not in the control group [13]. Similar sleep benefits following physical exercise were also evident in a more recent study [14], where we showed that jogging intervention had significantly improved sleep efficiency and sleep duration in children with ASD. More remarkably, we also observed that the endogenous melatonin level, as reflected by the 6-sulfatoxymelatonin (aMT6s), was significantly increased within the jogging intervention group, while no change was found in the control group. Physical exercise appears to be capable of modulating the endogenous melatonin level in children with ASD, which in turns improves their sleep quality. If it is so, it is then natural to ask which intervention (i.e. physical exercise or melatonin supplement of the combination of two) is more effective in treating sleep disturbance improving the sleep quality of children with ASD. Without direct comparison, this question remained unanswered. Therefore, here we propose a new study protocol.

This study protocol has two objectives: (1) to determine which intervention is more effective in improving sleep quality in children with ASD and 2) to explain how these interventions impact on sleep via melatonin-mediated mechanism model. We hypothesise that the combination intervention (i.e. jogging and melatonin supplement) is the most effective because it may provide sufficient melatonin level to enhance sleep quality through both physical exercise and melatonin supplement.

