### Statistical methods

All statistical analyses will be conducted using SPSS (version 26.0) for Windows (SPSS Inc., Chicago, IL, USA). All the data will be entered into SPSS by the research assistant. One-way (4 Groups: physical exercise vs melatonin supplement vs combined exercise and melatonin supplement vs placebo-control) analysis of variances (ANOVA) with repeated measures will be performed to compare changes in actigraphy data and endogenous melatonin level between and within groups over different time points (i.e. T1-T3). Post-hoc analyses will be performed when any significant difference both between- and within-group is found in any of the outcome variables. Bonferroni correction will be used to adjust the alpha levels. Depending on the proportion of missing data and the assumption of normality, multilevel regression or a generalized estimating equation (GEE) will also be used as a sensitive analysis to assess the effects of the physical exercise intervention, melatonin supplement, time effect, and their interaction with sleep outcomes and melatonin level outcomes if there is any missing data. Average time spent in both daily sedentary activity and MVPA at baseline will be used as covariates. Linear regression will be used to analyse the association between participant’s adherence to the intervention and the outcome variables as a secondary analysis. Mediation analysis will be conducted to examine the mediating effect of endogenous melatonin level at T2 on the relation between physical exercise and sleep at T3. Preacher and Hayes’ bootstrapping and conditional process modeling will be used to determine the significance of the mediating effect. A p-value of <0.05 will be considered statistically significant. Both proposal analysis and intention-to-treat analysis will be carried out. Demographic variables (e.g. age, sex, BMI) will be adjusted if they demonstrate clinically significant prognostic effects on the outcomes (with absolute correlation or Cohen’s d effect size of >0.2) for both main analysis and mediation analysis.

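### The stated 80% power fits an unadjusted 5% test; the Bonferroni-corrected pairwise tests have about 53–64% for one intervention versus control, and no effect size is given for the comparisons between interventions

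*Protocol article*

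**What the plan says.** The Sample size calculation section of the protocol article takes the effect of exercise on sleep from two previous studies, "corresponding to a Cohen’s *d* of about 0.9", and adds for melatonin: "We assumed that melatonin supplements have similar effects on sleep". From this, "A sample of 20 participants per group is computed by G*power software to achieve a power of 80" per cent, with "a level of significance of 5% and 95% confidence level". Allowing for 25% attrition, 25 per group are recruited, 100 in all. The section does not name the test entered in G*Power, makes no multiplicity adjustment, and gives no effect size for one active arm against another or for the combination.

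The Statistical methods section plans a four-group repeated-measures ANOVA, followed by post-hoc comparisons if it is significant. For these, "Bonferroni correction will be used to adjust the alpha levels". The number of comparisons is not stated.

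The Introduction gives the first objective as "to determine which intervention is more effective in improving sleep quality in children with ASD". It also states a directional hypothesis: "We hypothesise that the combination intervention (i.e. jogging and melatonin supplement) is the most effective".

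**The concern.** The power statement and the research question are about different comparisons. The sizing uses the benefit of an intervention at an unadjusted 5% level. The question is which intervention is better and whether the combination is best, and it will be answered by pairwise tests at a stricter level.

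A reader who trusts the 80% would treat a non-significant pairwise result as informative. The Discussion invites this: it says that if the three interventions prove equally effective, exercise can be offered as an alternative. No equivalence margin is given, and with the power shown below a non-significant difference between two active arms could not support that conclusion.

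**Working it through.** **Inputs from the protocol.** d = 0.9 for exercise, read as against control; melatonin similar; 20 evaluable per group; alpha 0.05; 25 recruited per group with 25% attrition, so 25 × 0.75 = 18.75 evaluable.

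**Assumptions, because the protocol is silent.** Two-sided tests; one outcome; d = 0.9 on the scale that is tested; a Bonferroni divisor of 6 (four groups give 4 × 3 / 2 = 6 pairs) or 3.

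**1. Reproducing the stated figure.**
- Two-sample t-test: noncentrality d × √(n/2) = 0.9 × √10 = 2.846; df = 38; critical t = 2.024; power 79.2%. The normal approximation gives 81.2%.
- Omnibus F test with means 0, 0.9, 0.9, 0.9 (SD 1): grand mean 0.675; noncentrality 20 × (0.675² + 3 × 0.225²) = 20 × 0.6075 = 12.15; df 3 and 76; power 82.4%. Here 19 per group already suffices.

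Both are consistent with 20 per group and 80%.

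**2. One intervention versus control after Bonferroni.** Same noncentrality, stricter critical value (exact noncentral t):

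| Alpha | n = 20 | n = 18.75 |
|---|---|---|
| 0.05 | 79.2% | 76.4% |
| 0.05/3 = 0.0167 | 63.5% | 59.9% |
| 0.05/6 = 0.0083 | 53.1% | 49.3% |

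Using the pooled ANOVA error raises the 53.1% only to 55.7%. For scale, 80% power at 0.05/6 would need 32 evaluable per group.

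**3. Jogging versus melatonin.** Both are given about the same effect against control, so the planning difference between them is about 0.9 − 0.9 = 0. The calculation specifies nothing to detect.

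**4. Combination versus the single interventions.** The extra effect of the combination over a single intervention is not stated, so it is shown as a range. Normal outcomes, SD 1, n = 20; the joint figures are simulated:

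| Assumed increment | Beats one, 0.05 | Beats one, 0.05/6 | Beats both, each at 0.05 | Beats both, each at 0.05/6 |
|---|---|---|---|---|
| 0.5 | 33.8% | 13.0% | about 19% | about 5% |
| 0.7 | 57.8% | 30.0% | about 42% | about 16% |
| 0.9 (fully additive) | 79.2% | 53.1% | about 68% | 36.5% |

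At 19 per group and the additive 0.9, the joint power is about 65% with each test at 0.05 and 33% with each at 0.05/6.

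**The case against.** Several stronger readings are tempting, and the protocol does not support them.

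- *The 80% must be for a single two-group t-test.* The test is not named, and an omnibus F test with equal active arms fits equally well. This does not rescue the plan: an omnibus test does not say which intervention is better, and that pattern of means sets every difference between active arms to zero.
- *The four-group analysis as a whole is underpowered.* It is not. As a single-time approximation, the omnibus test has 82% power with means 0, 0.9, 0.9, 0.9 and over 99% if the combination reaches 1.8. The shortfall is in the corrected pairwise tests.
- *The power is fixed at one low figure.* The divisor is not stated; six is the natural count, but three gives 64%. Every figure for the combination depends on an increment that the protocol does not give. Repeated measures or baseline adjustment could also raise power if d = 0.9 is not already on the change scale, and the protocol does not say.
- *Head-to-head power equals alpha.* That reads similar as exactly equal. The fair statement is that no difference was specified.
- *The cited studies showed no effect on sleep onset latency.* The sizing section credits them with one. For the second of them the Introduction says only "where we showed that jogging intervention had significantly improved sleep efficiency and sleep duration in children with ASD", but it presents these results as examples, so it does not exclude a latency effect. What is visible is that the sizing section lists sleep duration twice.

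What remains is that a finished calculation is given at an unadjusted level, for an effect other than those named in the objective and hypothesis. Deferring detail to an analysis plan does not explain that.

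**Conclusion.** The concern holds in a limited form. The 80% is reproducible, but only as an unadjusted 5% test at d of about 0.9. For the Bonferroni-corrected pairs the power at the protocol's own d and n is about 53% with six pairs or 64% with three, and about 49% or 60% after the assumed attrition. This rests on two-sided tests, one outcome, and d = 0.9 on the analysed scale.

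For the comparisons between interventions the protocol fixes no power at all. The additive case is near a best case for the combination unless the two treatments reinforce each other; smaller increments bring the corrected joint power down quickly. A non-significant jogging-versus-melatonin result would carry little information.

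**What to change.** 1. In Sample size calculation, name the test to which the 80% refers. State the power of the corrected pairwise tests beside it, with the divisor used and at the number expected to be evaluable.
2. Replace Bonferroni with Holm. It gives the same error control and is never less powerful, though it will not by itself restore 80%.
3. Pre-name the hypothesis as a joint claim on one named sleep outcome: combination better than jogging and better than melatonin, each at 0.05. Both must succeed, so these two contrasts need no alpha split. This covers one outcome only; the protocol lists four actigraphic sleep parameters and melatonin level as primary. Show the power over a range of increments (about 19% at 0.5 and 68% at 0.9, with 20 per group).
4. State that a non-significant jogging-versus-melatonin result will not be read as equal effectiveness, and amend the Discussion accordingly.
5. Correct the list of outcomes to which d = 0.9 is attributed.

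The cost is protocol and analysis-plan wording and a less favourable stated power. No extra participants are needed. These changes do not make the jogging-versus-melatonin comparison well powered; they only stop the protocol from implying that it is.

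### 25 recruited per group covers 20% attrition, not the stated 25%: at 25% attrition 18.75 per group remain, short of the 20 the plan requires

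*Protocol article*

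**What the plan says.** All the relevant figures are in the Sample size calculation section of the protocol article. It takes an effect from earlier exercise studies, a Cohen's d "of about 0.9) on improving sleep onset latency, sleep duration and sleep duration", and carries it over to the other active treatment: "We assumed that melatonin supplements have similar effects on sleep". From this, "A sample of 20 participants per group is computed by G*power software", "to achieve a power of 80% and a level of significance of 5"%. The allowance for losses follows directly: "Assuming 25% attrition rate, 25 participants per group will be recruited (i.e. the total number is 100").

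The order of the sentences makes the roles clear. Twenty per group is the number needed for the stated power, and 25 per group is the number recruited so that enough remain after losses. No other section of the article adjusts for attrition or restates the total.

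**The concern.** Three statements in this section cannot all be true: 20 per group are needed, 25% will be lost, and 25 per group will be recruited. Adding 25% to the required number is not the same as allowing for the loss of 25% of the recruited number. The first divides the extra participants by the 20 who are needed; the second counts the losses out of the 25 who enter.

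What is at stake is the total of 100, on which recruitment and the power statement both rest. If attrition runs exactly as planned, the trial ends below its own required number, and a reader who takes the 80% at face value is misinformed, though not by much.

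**Working it through.** **Inputs, all from the Sample size calculation section:** d about 0.9; power 80%; significance level 5%; 20 per group required; attrition 25%; 25 per group and 100 in total recruited. Four equal groups come from the study design statement in the abstract. Two things are not stated and are assumed here: that the calculation is a two-sample comparison of means, and that it is two-sided.

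**1. Reproducing the 20.** By normal approximation, n per group = 2 × (1.960 + 0.842)² / 0.9² = 19.4, rounded up to 20. The noncentral t calculation gives 20.4. Both agree with the stated 20, given that d is only approximate. A one-sided test would need 16 per group, so it is not the calculation reported.

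**2. Reproducing the 25.** 20 × (1 + 0.25) = 25, which matches the plan exactly. 20 / (1 − 0.25) = 26.7, rounded up to 27, does not match. The allowance was therefore applied by multiplication.

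**3. What remains at the stated attrition.**
- 25 × (1 − 0.25) = 18.75 per group; 100 × 0.75 = 75 in total.
- Required: 20 per group, 4 × 20 = 80 in total.
- Shortfall: 1.25 per group, 5 in total.
- Attrition that 25 per group can absorb while keeping 20: 1 − 20/25 = 20%.
- Recruitment that a 25% allowance needs: 27 per group, 4 × 27 = 108 in total. Check: 27 × 0.75 = 20.25.

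**4. Power at the remaining number.** Two-sided, 5%, d = 0.9, one unadjusted comparison. For the t-test with n per group, df = 2n − 2 and the noncentrality is 0.9 × √(n/2). For the normal approximation, power = Φ(0.9 × √(n/2) − 1.960).

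| n per group | t-test | Normal approximation |
|---|---|---|
| 20 | 79.2% | 81.2% |
| 19 | 77.0% | 79.2% |
| 18.75 | 76.4% | 78.7% |

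Seventy-five participants cannot split evenly over four groups; three groups of 19 and one of 18 is the nearest split (3 × 19 + 18 = 75). A comparison of 19 with 18 has 75.8% power by t-test, so the t-test range at 25% attrition is about 76–77%.

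**5. Loss due to the allowance alone.** By t-test, 79.2 − 76.4 = 2.8 points. By normal approximation, 81.2 − 78.7 = 2.5 points.

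**The case against.** The head-count itself cannot be defended, but several objections limit what may be built on it.

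*The test is not named.* This stands. The Statistical methods section plans a four-group repeated-measures ANOVA, not a t-test, so every power figure above is conditional. An ANOVA calculation does not obviously rescue the plan, however. A four-group ANOVA with an effect size f of 0.45 (an assumption, since the article gives no f) would keep about 90% power at 18.75 per group, but it would have 92% at 20 and so is not the calculation that produced 20 for 80%.

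*Dropouts may still contribute data.* This stands in part. Intention-to-treat analysis is mentioned, and multilevel or GEE models can use partial records, but those models are planned as a sensitivity analysis and the main analysis is the repeated-measures ANOVA. In any case, the allowance exists because losses are expected to reduce the usable sample.

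*Inflating by multiplication is common.* It may be, but it does not deliver the stated 20.

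A reader might also go further than the documents allow, in three ways.
- One might infer that the required number is itself wrong, because an exact t-test at d = 0.9 gives 79.2% at 20 and calls for 21. But d is given only as about 0.9; at d = 0.91, 20 per group gives 80.1%, and the normal approximation gives 20 directly. The stated 20 is reproduced within rounding.
- One might put the loss at 3 to 5 points below 80%. That figure mixes the rounding gap just described with the loss from attrition, which is 2.5 to 2.8 points.
- One might quote 74.6% as the resulting power. That needs 18 in both compared groups, whereas 75 remaining participants leave at most one group at 18 under a near-even split. Eighteen in every group would be 72 participants, or 28% attrition.

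**Conclusion.** The point holds as a correction to a stated figure. Without any assumption about the test, 25 per group is consistent with 20% attrition and not with 25%: at 25%, 18.75 per group remain against 20 required. A 25% allowance would need 27 per group, 108 in total.

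The consequence for power is conditional and modest. If the calculation was a two-sided two-sample comparison at d = 0.9 and 5%, power at the planned attrition is about 76–77% by t-test or about 79% by normal approximation, for one comparison with no multiplicity adjustment. Both are below 80%, but the part due to the attrition step is under 3 points. The attrition rate is itself a planning guess, and the design and analysis do not depend on it. The sentence should be corrected because the total relies on it, but the slip does not undermine the trial: should-fix.

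**What to change.** Keep the total at 100 and correct the sentence, for example: *Twenty-five participants per group (100 in total) allows for 20% attrition; at 25% attrition about 19 per group would remain, and power for a single unadjusted two-sided comparison would be about 76–79%.* Name the test and the sidedness used in G*Power, and replace the range by the single figure for that test.

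This costs one sentence and a slightly less favourable power statement, with no added participants or procedures. If the sponsor prefers to keep the 25% allowance, the number to recruit is 27 per group, 108 in total, which is 8 more participants.

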### Randomization

Participants will be randomly assigned to three intervention groups or a placebo-control group by a trained research staff using MS Excel randomization function. Block randomization with block size of 5 will be used for equal allocation ratios.

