**Study design:**

The proposed study will be a four-group randomised control trial (RCT) design, with equal allocation of participants to the three intervention groups and one control group.

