## Methods/Design

### Study design

The proposed study will be a single blinded four-group randomised control trial (RCT).

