#### Intervention A—Morning jogging group

The training protocol, assessment and instructional technique will be referenced on our previous protocol in children with ASD [17]. However, we will modify the frequency of the jogging sessions to suit the comparison with other intervention group (i.e. intervention B and C). This intervention will be a 10-week jogging program consisting of 50 sessions (5 sessions per week, 30 min per session) in each participating school. The increase of jogging sessions from the previous protocol [17] is to make the prescription equivalent to the melatonin supplement prescription for other interventions (B and C), which will be prescribed to the participants every day, according to the previous protocol [17]. Moreover, this is more close to the World Health Organization (WHO) recommendation that everyone should participate in physical exercise daily. Meanwhile, the jogging program is confined to morning sessions based on the favourable sleep outcomes from previous study [18]. To counteract the possible influence of natural sunlight exposure, all jogging sessions will be confined to indoor setting. Each intervention session will be administered by a trained research assistant assisted by student helpers. All the research staff (i.e. student helpers and research assistant) will be required to attend a workshop to standardize the procedure on implementing the intervention, as well as handling and motivating their ASD partners. Each session will be conducted in an identical format with 5 minutes of warm-up activities, followed by 20 minutes of jogging (intervention), and 5 minutes of cool-down activities. In the jogging activity, participants will be asked to jog side-by-side with the research staff around an activity circuit (57m x 50m) marked with 4 red cones. Participants are instructed to jog at a moderate intensity level. The intensity level of jogging will be measured by heart rate monitor (Polar H1). Considering the general low physical fitness of children with ASD, physical exercise with a heart rate above 50% of the maximum heart rate (subtracting the participant’s age from 220) is regarded as moderate intensity. Motivation techniques (e.g. verbal cue, visual chart, favourite post-intervention activity) will be used to enhance the compliance rate. Meanwhile, questionnaire will be given to the research staff assisting the jogging intervention to assess the adherence of the intervention at T2. The feasibility, community-viability and sustainability of the exercise intervention are confirmed with previous research experience and the cooperation of the participating schools. Since these intervention sessions are conducted in the morning hours before school start times, the participants may get less sleep time since they must arrive at school early enough to do the exercise. To ensure the participants to have sufficient sleep, they are strongly encouraged to go to bed earlier at night.

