### Blinding

The person analysing the sleep parameters and melatonin level will be blinded for the group assignment.

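### One small, published, fixed block size in a trial with visible arms would let some upcoming assignments be deduced if children enter one by one

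*Protocol article*

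**What the plan says.** The Randomization section of the protocol article has two sentences. The first gives the method and who carries it out: "Participants will be randomly assigned to three intervention groups or a placebo-control group by a trained research staff using MS Excel randomization function". The second gives the block rule: "Block randomization with block size of 5 will be used for equal allocation ratios". The abstract's study design paragraph sets the target, a trial "with equal allocation of participants to the three intervention groups and one control group".

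Study design calls the trial single blinded, and Blinding names who that is: "The person analysing the sleep parameters and melatonin level will be blinded for the group assignment". No one else is described as blinded. In the jogging arms, "participants will be asked to jog side-by-side with the research staff around an activity circuit", so those who deliver the sessions know who jogs. A placebo is described for the control group only.

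The article does not state whether children are randomised singly or in batches, or who recruits them.

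**The concern.** A block is a promise about how many of each arm appear in a run of fixed length. Anyone who knows the length and sees the earlier assignments can count what is left. Near the end of a block the next assignment can become certain. Here the length is single, small and printed in the article, and the arms that carry the heavier burden (50 morning sessions over 10 weeks) are visible.

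Staff who could foresee the next arm could choose which child to enter next, or delay a family thought unlikely to manage early sessions. The arms would then differ at baseline in ways that analysis cannot fully undo. Keeping the list itself hidden would not cure this, because the prediction comes from the rule and the visible arms. That is why the point concerns a rule the article states, and does not rest on detail it leaves out.

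**Working it through.** **Inputs.** Block size 5 (Randomization); four arms in equal numbers (abstract); 100 children, 25 per group, 20 evaluable per group (Sample size calculation). Assumed: sequential entry, and a guesser who knows the block rule and every earlier assignment.

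**The stated rule.** 5 / 4 is not a whole number, so a block of 5 cannot hold four arms equally. 100 / 5 = 20 blocks; doubling the same arm each time would give 40/20/20/20. The rule therefore has to be read in one of three ways, and each is worked below.

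**Formula.** For each position in the block, take the probability of the most likely arm given what has been seen, then average over positions. An assignment is certain when only one arm remains possible.

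1. *Four arms plus one extra slot, arm drawn at random.* Correct by position: 0.25, 0.30, 0.383, 0.55, 0.70. Sum 2.183; 2.183 / 5 = 44%. Only the fifth position can be certain, when the doubled arm has already appeared twice (probability 3/5): 0.6 / 5 = 12%.
2. *Four arms plus the same extra arm every time.* Correct: 0.40, 0.40, 0.433, 0.55, 1.00. Sum 2.783; 2.783 / 5 = 56%. Certain: the fifth position always, the fourth with probability 1/10: 1.1 / 5 = 22%.
3. *Five per arm, a block of 20.* Correct, by simulation: 41%. Certain: the final run of one arm averages 20 / 16 = 1.25 positions; 1.25 / 20 = 6%.

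**The obvious repair, a fixed block of 4.** (1/4 + 1/3 + 1/2 + 1) / 4 = 52% correct; 1/4 = 25% certain.

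| Rule | Correct guess | Certain |
|---|---|---|
| Chance | 25% | 0% |
| 5, extra arm varies | 44% | 12% |
| 5, extra arm fixed | 56% | 22% |
| 5 per arm (block of 20) | 41% | 6% |
| Fixed 4 | 52% | 25% |
| Fixed 8 | 46% | 14% |
| Fixed 12 | 43% | 10% |
| Mixed 4/8/12, undisclosed | 46% | none held as certain |

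The rows for 8, 12 and mixed blocks are simulated. In the mixed row the guesser names the arm with the fewest children so far.

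**If staff can tell only jogging from no jogging.** Under reading 1, the next child's jogging status is certain in position 4 with probability 0.1 and in position 5 with probability 0.4: 0.5 / 5 = 10%. With a fixed block of 4 it is (1/3 + 1) / 4 = 33%.

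**What steering could do (illustration only).** Suppose children 0.5 SD better fill every certain slot of one arm and children 0.5 SD worse fill those of another. The bias is 2 x 0.5 x the certain share: about 0.06, 0.12 and 0.22 SD for readings 3, 1 and 2, and 0.25 SD for a block of 4. With 20 per group, noncentrality is bias x sqrt(20/2), and a two-sided t-test of a null effect rejects as follows:

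| Bias (SD) | Unadjusted, nominal 5% | Bonferroni over six pairs, nominal 0.05/6 = 0.8% |
|---|---|---|
| 0.06 | 5.4% | 0.9% |
| 0.12 | 6.6% | 1.3% |
| 0.22 | 10.4% | 2.5% |
| 0.25 | 12.0% | 3.0% |

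The Statistical methods section plans Bonferroni-corrected post-hoc comparisons, so the right-hand column is nearer the plan. Six pairs is an assumption.

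**The case against.** The strongest objection is that the deduction needs sequential entry, which the article does not state. School-based assessment weeks, a programme run in each participating school and a T2 timed from the start of the study fit cohort allocation at least as well. Allocating everyone in one draw after T1 would remove the effect altogether. This stands, and it is why the point is conditional.

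A reader might also infer that the allocator is one of the people who deliver the jogging and holds the list, because the jogging section says "All the research staff (i.e. student helpers and research assistant) will be required to attend a workshop to standardize the procedure on implementing the intervention" and the allocation is done "by a trained research staff using MS Excel randomization function". The documents do not support that. The definition appears in the section on delivering the jogging. The Randomization section does not say that the allocator delivers, recruits or keeps the list. Custody and concealment are details a condensed article may leave to the full protocol.

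A reader might further infer that the trial's error rate would rise to 7% to 12%. That comes from an unadjusted test under deliberate, opposite steering into every certain slot, and leaves out the five-per-arm reading. Of the three readings, that one alone guarantees equal groups, and it gives 5.4%. With the planned correction the rates are about 1% to 3% against 0.8%. Analysing change from T1 would also offset part of any steering on baseline sleep, though not steering on expected compliance.

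Finally, varied blocks barely change guessing: 46% is below the 52% and 56% above, but not below 44% or 41%. This also stands. The gain lies in the certain assignments.

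**Conclusion.** The point holds as a weakness in a stated rule. Under every workable reading of the block of 5, a guesser who sees earlier assignments beats the 25% chance rate (41% to 56% correct) and knows 6% to 22% of assignments outright. The size rests on three assumptions: children enter one at a time, staff know the earlier arms, and someone with that knowledge influences who enters next. The article settles none of them. Selection bias is therefore possible and not demonstrated, and with a single draw after T1 it would be nil.

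It is worth acting on because the sentence must be rewritten anyway, since a block of 5 cannot give four equal arms. The most natural correction, a fixed block of 4, would leave more assignments certain (25%) than any reading of the present text.

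**What to change.** Replace the block rule in the Randomization section with one of these:

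- Permuted blocks whose sizes vary at random among multiples of 4 (for example 4, 8 and 12). The sizes are not disclosed to recruiting or delivery staff and are left out of the published article. The list is generated by an existing colleague with no part in recruitment or delivery.
- One draw for each recruited batch, made only after consent and the T1 assessment are complete for every child in that batch.

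State in either case whether entry is sequential or by batch. If allocation has already begun, record how it was done so that readers can judge the risk.

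The cost is one paragraph of amendment and a short script. No extra participants or procedures are needed. Balance is slightly looser while a larger block is open: two arms can differ by up to 12 / 4 = 3 within a block of 12, against 1 within a block of 4. The first option mainly removes certain assignments and leaves guessing near 46%. The second removes the opportunity within each batch.
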